## 8.3 Endpoint Definitions

### 8.3.1 Primary Endpoint

The primary objective is to determine the MTD and safety profile of SGI-110 in combination with ipilimumab in 21 day cycles in melanoma patients. Endpoints related to this objective include an evaluation of DLTs, overall safety and parameters related to the MTD. The MTD evaluation will be based on the DLT evaluable population. Endpoints for safety profile include an evaluation of AEs, SAEs, laboratory evaluations, vital signs and physical examination.

### 8.3.2 Secondary Endpoints

#### 8.3.2.1 Secondary Efficacy Endpoints based on immune-related Response Criteria

Tumor assessment, using the immune-related response criteria (ir-RC), is made by the investigator.

Immune-related Disease Control Rate (irDCR) is the proportion of treated subjects with an ir-BOR of confirmed irCR, confirmed irPR or irSD.

Immune-related Objective Response Rate (irORR) is the proportion of treated subjects with a irBOR of confirmed irCR or confirmed irPR.

Immune-related Time to Response (irTTR) is defined as the time from first dosing date until the measurement criteria are first met for overall response of irPR or irCR (whichever status comes first, and provided it is subsequently confirmed).

Immune-related Duration of Response (irDoR) for the subjects whose irBOR is irCR or irPR will be defined as the time between the date of response of confirmed irCR or confirmed irPR (whichever occurs first) and the date of irPD or death (whichever occurs first). The onset of a confirmed irCR or irPR is determined by the initial assessment of response, not by the confirmatory assessment. Note that if an assessment of irPR occurs before confirmation of irCR, the duration of immune-related response endpoint will not begin at the time that the irBOR of irCR is shown but rather at the earlier time-point showing irPR. For subjects who remain alive and have not progressed following response, irDoR will be censored on the date of last evaluable TA.

#### 8.3.2.2 Immune-related Progression-free Survival (irPFS)

Immune-related progression free survival (irPFS) per irRC will be defined as the time between the date of randomization and the date of progression per irRC or death, whichever occurs first. A subject who dies without reported progression per irRC will be considered to have progressed on the date of death. For those subjects who remain alive and have not progressed, irPFS will be censored on the date of last evaluable TA. For those subjects who remain alive and have no recorded post baseline TA, irPFS will be censored on the day of last clinical evaluation.

### 8.3.3 *Exploratory Endpoints*

#### *Translational Research*

- For a detailed workplan of translational studies see **Appendix A**,
- The analysis of these data will be performed with a prospective exploratory intent. No formal hypotheses testing is planned,
- Characterize the pharmacokinetic profile of SGI-110 and decitabine. For a detailed workplan of pharmacokinetic analyses see **Appendix B**.

## 8.4 **Analyses**

### 8.4.1 *Demographics and Baseline Characteristics*

Demographic and baseline characteristics will be summarized for all subjects using descriptive statistics by treatment arms and overall for the FAS set. Categorical data will be presented as frequencies and percentages. For continuous data, mean, standard deviation, median, 25th and 75th percentiles, minimum and maximum will be reported.

### 8.4.2 *Safety Analyses*

Reporting of safety, extent of exposure, concomitant medications and discontinuation of study therapy will be based on all treated subjects; for on-study laboratory test results, all treated subjects with at least one on-study laboratory measurement available will be included in the analysis. The reporting period for safety data will be from the date of first dose received on this study to 70 days (5 half-lives) after the last dose is received. Serious adverse events are reported from the time of consent forward for all subjects.

The analysis of safety will be based on the frequency of AEs and their severity for all treated subjects. Worst toxicity grades per subject will be tabulated for AEs and on-study laboratory measurements by using the NCI CTCAE version 4.0. Additionally, immune-related (ir) see Section 1.3.5.3, drug-related and serious AEs will be tabulated separately, and listings by subject will be produced for all deaths, all SAEs and all AEs leading to discontinuation of study drug.

Assessment of extent of exposure will include tabulation of dose omissions, reductions and delays.

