**Safety Assessment:**

The analysis of safety will be based on the frequency of the adverse events and their severity for all treated patients. Worst toxicity grades *per* patient will be tabulated for adverse events and laboratory measurements using the NCI CTCAE v.4.0.

The analysis of safety will be based on the frequency of the adverse events and their severity for all treated patients. Worst toxicity grades per patient will be tabulated for adverse events and laboratory measurements using the NCI CTCAE v.4.0. The risk/benefit relationship will be assessed.

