#### ***Target Population***

- 1) Subjects must fulfill all of the following inclusion criteria:
- 2) Unresectable Stage III or Stage IV melanoma with measurable lesions by CT or MRI per mWHO/irRC criteria, that can be amenable to biopsy

- 3) Previously treated or untreated; prior therapy may include chemotherapy or targeted therapy for metastatic disease (i.e., BRAF and/or MEK inhibitor). Prior adjuvant interferon is permitted.
- 4) Subjects with ECOG performance status of 0 to 1
- 5) 4 weeks or greater since last treatment
- 6) Must have recovered from any acute toxicity associated with prior therapy
- 7) Life expectancy greater than 16 weeks
- 8) Subjects with adequate organ function defined as:
  - 9) WBC  $\geq 3500/\mu\text{L}$
  - 10) ANC  $\geq 2000/\mu\text{L}$
  - 11) Platelets  $\geq 100 \times 10^3/\mu\text{L}$
  - 12) Hemoglobin  $\geq 9 \text{ g/dL}$
  - 13) Creatinine  $\leq 2.5 \times \text{ULN}$
  - 14) AST  $\leq 2.5 \times \text{ULN}$  for patients without liver metastasis  
 $\leq 5 \times \text{ULN}$  for patients with liver metastasis
  - 15) Bilirubin  $\leq 1.5 \times \text{ULN}$  for patients without liver metastasis  
 $\leq 3 \times \text{ULN}$  for patients with liver metastasis  
 $<3.0 \text{ mg/mL}$  for patients with Gilbert's Syndrome
- 16) Negative screening tests for HIV, HepB, and HepC. If positive results are not indicative of true active or chronic infection, the patient can enter the study after discussion and agreement between the Investigator and the Medical Monitor.
- 17) Women of child-bearing potential must not be pregnant or breastfeeding, must have a negative pregnancy test at Screening and all men must be practicing two medically acceptable methods of birth control. Men should not father a child while receiving treatment with SGI-110 + ipilimumab, and for 2 months following completion of treatment. Men with female partners of childbearing potential should use effective contraception during this time.

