### ***Dose Delay Criteria for ipilimumab***

Because of the potential for clinically meaningful ipilimumab-related AEs requiring early recognition and prompt intervention, management algorithms have been developed for suspected AEs of selected categories.

Subjects may resume treatment with study drug when the drug-related AE(s) resolve to Grade  $\leq 1$  or baseline value, with the following exceptions:

- Subjects may resume treatment in the presence of Grade 2 fatigue,
- Subjects who have not experienced a Grade 3 drug-related skin AE may resume treatment in the presence of Grade 2 skin adverse event,
- Subjects with baseline Grade 1 AST/ALT or total bilirubin who require dose delays for reasons other than a 2-grade shift in AST/ALT or total bilirubin may resume treatment in the presence of Grade 2 AST/ALT OR total bilirubin,
- Subjects with combined Grade 2 AST/ALT AND total bilirubin values meeting discontinuation parameters should have treatment permanently discontinued,
- Drug-related pulmonary AEs, diarrhea, or colitis, must have resolved to baseline before treatment is resumed,
- Drug-related endocrinopathies adequately controlled with only physiologic hormone replacement may resume treatment.

Dose delay criteria apply for all drug-related adverse events (regardless of whether or not the event is attributed to ipilimumab). All study drugs must be delayed until treatment can resume.

If the criteria to resume treatment are met, the subject should restart treatment at the next scheduled timepoint per protocol. However, if the treatment is delayed past the next scheduled timepoint per protocol, the next scheduled timepoint will be delayed until dosing resumes. If treatment is delayed  $> 6$  weeks, the subject must be permanently discontinued from study therapy, except as specified below.

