### ***6.3.1 Medical History, Physical Exam, Physical Measurements***

A detailed Medical History will be obtained at Screening. Medical history must include date of diagnosis, including histological or cytological documentation of malignancy. Any toxicity related to previous treatments should be mentioned, if applicable.

A complete physical examination including subject's height and weight will be performed at Screening. Prior to dosing (within 3 days), the subject's weight must be obtained to calculate the ipilimumab dose and the subject's body surface area on which SGI-110 dose is calculated.

If the Screening physical exam is conducted within 24 hours of dosing on Week 0, then a single examination may count as both Screening and Pre-dose examination. Subsequent physical exams will be performed if clinically indicated. Any physical examination finding that qualifies as an AE or SAE must be documented on the appropriate CRF pages. Pre-treatment events present within 2 weeks of starting therapy, whether or not related to current disease, will be captured prior to the study start. Any worsening ( $\geq 1$  Grade from Baseline) will be documented as an AE in the CRF.

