## 7 ADVERSE EVENTS

### 7.1 Definitions

An Adverse Event (AE) is defined as any new untoward medical occurrence or worsening of a pre-existing medical condition in a patient or clinical investigation subject administered an investigational (medicinal) product and that does not necessarily have a causal relationship with this treatment. An AE can therefore be any unfavorable and unintended sign (including an abnormal laboratory finding, for example), symptom, or disease temporally associated with the use of investigational product, whether or not considered related to the investigational product.

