Toxicity will be reported according to National Cancer Institute-Common Toxicity Criteria (NCI CTC) version 4.0 (2004) criteria. The safety analysis population will include all subjects who receive at least one dose of drug. Subjects will be assigned to treatment groups as treated. In tables showing the overall incidence of AEs, subjects who experienced the same event on more than one occasion are counted only once in the calculation of the event frequency.

All safety parameters will be summarized and presented in tables based on this safety population.

Demographic and baseline characteristics will be summarized for all treated subjects using descriptive statistics. Reporting of safety, extent of exposure, concomitant medications and discontinuation of study therapy will be based on all treated subjects. Worst toxicity grades per subject will be tabulated for AEs and on-study laboratory measurements by using the National Cancer Institute (NCI) Common Terminology Criteria for Adverse Events (CTCAE) version 4.0.

- Translational studies
- For a detailed work plan of translational studies see **Appendix A**

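### The laboratory safety table gives the worst on-study grade without the baseline grade, so it cannot separate pre-existing from treatment-emergent abnormality

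*Combined protocol and SAP*

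**What the plan says.** Section 8.4.2 (Safety Analyses) specifies the laboratory summary in one sentence: "Worst toxicity grades per subject will be tabulated for AEs and on-study laboratory measurements by using the NCI CTCAE version 4.0". Section 8.1 and the statistical part of the synopsis repeat it in nearly the same words. The synopsis paragraph on safety assessment says the same without the term on-study.

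Under 8.4.2, a treated patient enters the laboratory analysis with a single on-study value, and no baseline value is required. The safety reporting period opens on the date of first dose.

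Section 8.3.1 makes laboratory data part of the primary endpoint: "Endpoints for safety profile include an evaluation of AEs, SAEs, laboratory evaluations, vital signs and physical examination".

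Section 4.2.1 allows the following at entry:
- creatinine up to 2.5 x ULN;
- AST up to 2.5 x ULN, or 5 x ULN with liver metastases;
- bilirubin up to 1.5 x ULN, or 3 x ULN with liver metastases;
- hemoglobin from 9 g/dL.

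The ipilimumab dose-delay rules in section 5.3.1 make provision for "Subjects with baseline Grade 1 AST/ALT or total bilirubin".

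**The concern.** A worst-grade table is read as a table of toxicity. That reading is safe only if patients start without graded abnormalities or if the starting grade is shown beside the worst one. Here the entry criteria admit abnormal values, and the dose-delay rules provide for graded ones. A stable abnormality caused by liver metastases or earlier therapy would appear under a worst toxicity grade and could be taken for an effect of the combination.

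The study has no control arm from which to judge the background level. It treats at most 19 patients, so two or three stable abnormalities would visibly change a table row. The protocol uses baseline in its dosing rules: section 5.3.1 judges recovery against eligibility levels or the patient's baseline status, and it refers to a 2-grade shift in AST/ALT or bilirubin. The analysis section does not carry this over.

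**Working it through.** The plan states no figure on this point, so there is none to reproduce. The check is mainly a reading of the safety and laboratory sections, followed by arithmetic on stated assumptions.

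**1. Is a baseline comparison planned anywhere?** Sections 8.1, 8.3.1, 8.4.1 and 8.4.2 and the synopsis contain no baseline-grade column, shift table, change from baseline or definition of a treatment-emergent laboratory abnormality. Section 8.4.1 summarises baseline characteristics for the group. It does not name laboratory grades, and a group summary cannot be linked to each patient's worst grade.

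**2. What does the table do with two different patients?** Patient A has liver metastases, enters with AST at 4 x ULN (allowed, since the limit is 5 x ULN) and stays there. Patient B rises from normal to 4 x ULN. Their worst on-study values are equal, so their grades are equal and they fall in the same cell. No CTCAE cut-point is needed for this, and the documents give none.

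**3. What can the table alone tell us?** If k patients show a worst grade of 1 or more for a test, the number who worsened on treatment can be anything from 0 to k.

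**4. How large could the mixing be?** Let p be the share entering with a graded value for a given test, w the share of those who worsen by at least one grade, and q the share of the others who become graded on treatment. None of these is in the documents, so all values below are assumptions. The sample size of 6 to 19 is from the synopsis.

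Entering graded, n x p, with p from 0.10 to 0.40:
- n = 19: 19 x 0.10 = 1.9 and 19 x 0.40 = 7.6
- n = 6: 6 x 0.10 = 0.6 and 6 x 0.40 = 2.4

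Entering graded and not worsening, 19 x p x (1 - w), with w from 0.25 to 0.75:
- lowest: 19 x 0.10 x 0.25 = 0.48
- highest: 19 x 0.40 x 0.75 = 5.7

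These are upper bounds on the non-emergent count, because a patient whose values normalise at every post-dose sample leaves the graded rows.

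Illustration with p = 0.20, w = 0.25, q = 0.20 and n = 19:
- shown as graded: 19 x (0.20 + 0.80 x 0.20) = 19 x 0.36 = 6.84
- treatment-emergent: 19 x (0.80 x 0.20 + 0.20 x 0.25) = 19 x 0.21 = 3.99
- not worsened: 19 x (0.20 x 0.75) = 19 x 0.15 = 2.85

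In this example 2.85 / 6.84, or about 42%, of the patients shown as graded did not worsen on treatment.

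**The case against.** The strongest reply is that the distinction is largely drawn in the adverse event data. Section 7.1 defines an adverse event as "any new untoward medical occurrence or worsening of a pre-existing medical condition", and this can include an abnormal laboratory finding. Section 6.3.1 has any worsening of at least one grade from baseline recorded as an adverse event. Section 7.5 sends certain laboratory results to the adverse event page: those that are clinically significant or serious, that cause interruption or discontinuation, or that need corrective therapy. Drug-related events are tabulated separately. This stands in part. However, the one-grade rule sits in the history and physical examination section and its reach to laboratory values is not stated, section 7.5 covers only selected results, and neither changes the laboratory table.

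A second reply is that the gravest values cannot be mistaken for entry values. Entry requires ANC of at least 2000/µL, four times the DLT neutrophil threshold of 0.5 x 10⁹/L. The single-test limits for stopping ipilimumab (AST above 8 x ULN, bilirubin above 5 x ULN) lie above the entry ceilings. That is correct, and it confines the ambiguity mostly to less extreme values. One overlap remains: the combined stopping criterion (AST or ALT above 3 x ULN with bilirubin above 2 x ULN) lies within the entry range allowed with liver metastases, although it applies only to drug-related abnormalities.

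Third, section 8.1 promises tables of all safety parameters, and section 8.4.3 refers to a Statistical Analysis Plan that could add a shift table. The first statement does not specify a baseline comparison. The second concerns prognostic factors only. A later plan may fill the gap, but the text available does not.

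Finally, dose decisions do not depend on this table. A DLT is a listed event clearly related to treatment, and the Safety Monitoring Committee receives the full laboratory data from at least the first three weeks. This stands and limits the weight of the point.

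**Conclusion.** The point holds. As specified, the laboratory table counts a stable pre-existing abnormality under a worst toxicity grade and cannot separate it from one that arose or worsened on treatment. That conclusion follows from the table's construction and the entry criteria, and it needs no assumed number.

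The size is not known. Under the assumed ranges, up to about 0.5 to 5.7 of 19 patients per test would be shown as graded without having worsened. These figures illustrate the scale and are not estimates.

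The consequence is limited to the reading of one descriptive table within the primary safety endpoint. DLT and MTD decisions are largely unaffected, and no data are lost. This is a worthwhile minor improvement, not a flaw in the design.

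**What to change.** In sections 8.1 and 8.4.2, and in the matching synopsis text, add for each graded laboratory test:
- a cross-tabulation of baseline grade against worst post-dose grade, with baseline defined as the last value before the first dose, including the Week 0 pre-dose sample;
- the number and percentage of patients who worsen by at least one grade;
- a separate row for patients with no baseline value.

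Keep the worst-grade column alongside.

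The cost is a few extra tables. The schedule in section 6.1 already has chemistry and hematology at Screening and before dosing at Week 0, and section 7.5 puts all laboratory values on the CRF. No new sample, visit or CRF page is needed.

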### 8.4.3 *Efficacy Analyses*

Analyses of efficacy endpoints will be based on all treated subjects (FAS set). The secondary efficacy endpoints will be evaluated with an explorative intent. The efficacy endpoints ir-DOR, ir-TTR will only be estimated for subjects with a confirmed best overall response of CR or PR. Exact two-sided 95% Confidence Intervals (CI) will be calculated using the binomial method for the proportion endpoints ir-DCR, ir-ORR.

OS will be estimated using Kaplan-Meier Product Limit method. A two-sided 95% confidence interval for the median survival will be computed using the Brookmeyer and Crowley method. PFS, ir-DOR, and Brain-PFS will be analyzed similarly.

OS will be further described using the survival rate, defined as the probability that a subject is alive at 6, 12, 18 and 24 months following date of the first treatment dose and estimated via the Kaplan-Meier method. A corresponding two-sided 95% confidence interval will be calculated.

Ir-TTR will be summarized using descriptive statistics.

A Cox regression analysis will be performed to adjust treatment effect for prognostic factors. Prognostic factors will be identified, before analysis, in the Statistical Analysis Plan.

### ***Pharmacokinetic Analyses***

Characterize the pharmacokinetic profile of SGL-110 and decitabine. For a detailed workplan of pharmacokinetic analyses see **Appendix B**.

#### ***8.4.4 Translational Research***

For a detailed workplan of translational studies see **Appendix A**.

### **8.5 Interim Analyses**

No interim analysis for efficacy will be conducted.

## **9 ADMINISTRATIVE SECTION**

### **9.1 Compliance**

#### ***9.1.1 Compliance with the Protocol and Protocol Revisions***

The study shall be conducted as described in this approved protocol. All revisions to the protocol must be discussed with, and be prepared by, Fondazione NIBIT. The investigator should not implement any deviation or change to the protocol without prior review and documented approval/favorable opinion from the IRB/IEC of an amendment, except where necessary to eliminate an immediate hazard(s) to study subjects. Any significant deviation must be documented in the CRF.

If a deviation or change to a protocol is implemented to eliminate an immediate hazard(s) prior to obtaining IRB/IEC approval/favorable opinion, as soon as possible the deviation or change will be submitted to:

- IRB/IEC for review and approval/favorable opinion,
- Fondazione NIBIT/CRO,

Regulatory Authority(ies), if required by local regulations,

Documentation of approval signed by the chairperson or designee of the IRB(s)/IEC(s) must be sent to Fondazione NIBIT/CRO.

If an amendment substantially alters the study design or increases the potential risk to the subject: (1) the consent form must be revised and submitted to the IRB(s)/IEC(s) for review and approval/favorable opinion; (2) the revised form must be used to obtain consent from subjects currently enrolled in the study if they are affected by the amendment; and (3) the new form must be used to obtain consent from new subjects prior to enrollment.

If the revision is an administrative letter, investigators must inform their IRB(s)/IEC(s).

### **9.1.2 Monitoring**

Representatives of Fondazione NIBIT/CRO must be allowed to visit all study site locations periodically to assess the data quality and study integrity. On site they will review study records and directly compare them with source documents, discuss the conduct of the study with the investigator, and verify that the facilities remain acceptable.

In addition, the study may be evaluated by Fondazione NIBIT and government inspectors who must be allowed access to CRFs, source documents, other study files, and study facilities. NIBIT audit reports will be kept confidential.

THE INVESTIGATOR MUST NOTIFY FONDAZIONE NIBIT/CRO PROMPTLY OF ANY INSPECTIONS SCHEDULED BY REGULATORY AUTHORITIES, AND PROMPTLY FORWARD COPIES OF INSPECTION REPORTS TO FONDAZIONE NIBIT/CRO.

